### Study procedures

This cross-sectional observational study, **B**lack women’s **L**ife experience **O**n cardiovascular health via **O**ngoing **M**onitoring (BLOOM), will involve two in-person visits at UTA with a 10-day ambulatory monitoring at participants’ free-living environments. The primary purpose of the first visit is to conduct the lab-based physiological assessments (i.e., a fasted blood draw and peripheral & cerebral vascular function/health) and provide the ambulatory assessment tools and associated instructions to participants (i.e., a wrist-worn accelerometer, a wrist-worn blood pressure monitor, a smartphone application [app], and a saliva self-collection kit). The study principal investigator is [name], [name] from UTA. Drs. [name] from UTA and [name] from Arizona State University are the study co-investigators. [name] from UTA, a board member of the Tarrant County Health Equity Alliance, served as the subject matter expert during the first year of the study (to assist with study protocol design based on her expertise and experience working and interacting with the community members). Our study protocol followed the Standard Protocol Items for Observational Studies (SPIROS) [35] guideline (see appendix). The first version of this study protocol was reviewed and approved by the UTA’s Institutional Review Board (protocol #: 2023 − 0344) on September 27, 2023. Continuing review will be performed by the IRB annually. Any serious adverse events and unanticipated problems will be reported to this institutional IRB. Amendments to the protocol will be reviewed and approved by the IRB before implementation. Because this is an observational study that involves minimal risks, a data monitoring committee is not needed. All study staff will be trained by the investigator team prior to conducting any study-related activities. We keep a detailed standard of operating procedure document that covers all aspects of study-related activities, from participant recruitment to data collection and management, to ensure study quality and consistency. This study is registered on ClinicalTrials.gov (NCT06150989, registration date: November 30, 2023).

Eligible participants will be scheduled for an in-person visit at the Physical Activity and Wearable Sensors (PAWS) Research Laboratory, located at the UTA campus in Arlington, Texas. At this in-person visit, a study staff will first provide a throughout overview of the study purposes, all study-related procedures and the potential related risks, and study compensation plan. Since this study will involve collection of blood samples from Black women, we followed the recommended guidelines to ensure a transparent process and trustworthy discussion between the research staff and study participants [36]. After this study overview and allowing participants to ask any questions they might have, participants will provide a written informed consent by signing an informed consent document for their enrollment in the study. The ambulatory monitoring period will start on the first day following the lab-based assessments (i.e., Visit #1) and will last a total of 10 days. Participants will be instructed to follow their usual behaviors and routines during this period. They will wear the accelerometer (ActiGraph wGT3X-BT) on their non-dominant wrist, wear the blood pressure wristband (Aktiia SA) on their dominant wrist, and answer 6 brief electronic surveys each day via a smartphone app. They will provide four saliva samples a day for 3 consecutive days out of the 10-day period.

At the end of the 10-day monitoring period, participants will return the study devices and all collected saliva samples. They will also complete a brief exit survey to share their opinions and feedback about this study. To encourage study procedure adherence, participants will be compensated for their time and effort on a pro-rated basis. In total, participants will receive up to $150 for completing all study procedures. Participants can stop taking part in the study at any point during the study period. In that scenario, participants will be compensated based on the study components they have completed. All study data will be kept confidential. The participants’ full names or personally identifiable information will not be requested on any study materials. Each participant will be assigned a study ID that links their data from online surveys, ambulatory monitoring devices, lab assessments, and biomarker assay data.

### Lab-based assessments (procedures and measures)

The following assessments of cardiovascular health indicators will take place during participants’ in-person study visit.

A fasting venous blood sample will be taken for assessment of a comprehensive metabolic panel (e.g., glucose, glycated hemoglobin, blood lipid profile, etc.), as well as biomarkers associated with CVD risk [37], including markers of inflammation (e.g., CRP & vascular cellular adhesion molecule-1 [VCAM-1]), oxidative stress (e.g., thiobarbituric acid reactive substances [TBARS] & superoxide), and antioxidant status. Individual assays will be performed via enzyme-linked immunosorbent assay kits. Reactive oxygen species will be measured using electron paramagnetic resonance spectroscopy and superoxide fluorescence via peripheral blood mononuclear cells as previously described [38].

*Cerebral vascular function/health* will be measured utilizing trans-cranial Doppler ultrasound assessment of blood velocity in the middle cerebral artery (MCAv_mean_) and Doppler ultrasound measures of blood flow in the extracranial arteries (e.g., internal carotid artery [ICA]) during a hypercapnic challenge induced by breathing 6% Carbon dioxide. Cerebral function/health will be defined as the % increase and slope of the response in MCAv_mean_, ICA_flow_, and ICA or MCA conductance from baseline during hypercapnia. This methodological approach is routinely performed in our laboratory [39, 40]. Importantly, this is predictive of and a contributor to various neurocognitive conditions and cerebral vascular diseases [41, 42].

*Peripheral vascular function/health* will be determined by several commonly utilized approaches. Macrovascular function will be assessed as brachial artery vasodilation following a period of suprasystolic cuff occlusion (i.e., flow-mediated vasodilation). Microvascular function will be assessed as the % change in blood velocity from baseline following cuff release. Large elastic artery health will be assessed as carotid artery intima-media thickness as well as central and peripheral artery ß-stiffness, arterial compliance, and pulse wave velocity utilizing Doppler ultrasound (GE P5) and applanation tonometry (SphygmoCor® CPV Pulse Wave Velocity System). This is critical as impairments in these variables contribute to cerebral vascular dysfunction as well as other forms of CVD [43, 44].

### Ambulatory assessments (procedures and measures)

*The 24-h Movement Behaviors* We will use the ActiGraph wGT3X-BT device to obtain measures of physical activity, sedentary behavior, and sleep. This device is a water-resistant, triaxial accelerometry that is used widely to capture continuous, high-resolution movement behaviors. Participants will wear the ActiGraph device on their non-dominant wrist at all times for 10 days. Collected data will be stored in the ActiGraph device’s internal memory and will be downloaded upon device returned at visit 2. We will apply the cut-points developed for wrist-worn ActiGraph accelerometer to define light-intensity activity, moderate-to-vigorous intensity activity, and sedentary behavior. We will follow the standard protocol to obtain sleep estimates from ActiGraph, which includes measures of sleep onset latency (SOL), time spent awake after sleep onset (WASO), and total sleep time (TST). In addition, we will use the daily electronic survey to capture self-reported sleep information to complement the ActiGraph-measured sleep data (e.g., to adjust sleep-awake time detected by ActiGraph as needed and obtain more information about perceived sleep quality). In the first daily electronic survey, adapted items from the Pittsburgh Sleep Diary will be included to capture self-reported sleep duration, sleep efficiency, and sleep quality [45].

*Daily Experience* We will use mobile-based ecological momentary assessment (EMA) to capture daily experiences. EMA is a brief survey designed to repeatedly assess individuals’ daily events, experience, and contexts multiple times a day to obtain “snapshots” of their everyday lives [46]. The EMA survey will be administered via a smartphone app, mEMA (illumivu). Illumivu is a commercially available EMA platform widely used by behavioral science researchers. EMA surveys will be prompted up to 6 times, at random intervals throughout the day, for 10 days. The random prompt window will be calculated by dividing the waking period (i.e., from participant’s typical wake time to typical bedtime) by 6, and one EMA survey will be prompted/delivered randomly during each time window. All EMA survey items to be used have been carefully selected from relevant previous studies. To capture *perceived racial discrimination and microaggression*, we will use adapted items from the Experiences of Discrimination (EOD) [47] and Gendered Racial Microaggressions Scale (GRMS) [48]. As in previous EMA studies [49], items for *mood/affective states* are chosen based on the two fundamental dimensions of affect suggested by the circumplex model (i.e., positive and negative affect). *Perceived stress* will be assessed using two items from the Perceived Stress Scale [50]. Each EMA survey will take no more than 3–5 min to complete. Responses to the EMA surveys will be automatically uploaded to the illumivu’s cloud-based server, and will be download for data analysis upon data collection completion.

*Salivary Cortisol* Saliva samples will be collected four times a day (i.e., at wakeup, 30 min after waking, before dinner, and right before bedtime) for 3 consecutive days (2 weekdays and 1 weekend days) to capture diurnal patterns of stress across the day. We will follow the collection procedures that have been used in previous studies that demonstrated high feasibility in women [51, 52]. We will use the Salivette device (Sarstedt, Inc.), a small, cotton dental sponge swab. Participants will be asked to place the swab in their mouth for 2 min and to store the samples in their home freezer as soon as possible after each collection. At the end of the 10-day study period, we will retrieve all saliva tubes from each participant and store them at a -80ºC freezer until they are assayed in batches.

*Continuous Blood Pressure* To obtain additional insights regarding participants’ daily blood pressure pattern, we will use a wrist-worn continuous blood pressure device (Aktiia) to supplement our lab-based assessments. The Aktiia bracelet automatically tracks blood pressure throughout the day and has been clinically validated for accuracy [53, 54]. It is a wearable CE-marked Class IIa medical device that records optical signals at the wrist and transforms them into the blood pressure values using pulse wave analysis algorithms after an initial calibration procedure based on a series of oscillometric measurement performed by an upper arm cuff [55]. The Aktiia bracelet can provide up to 12 blood pressure readings each day. All data will be uploaded wirelessly through an Aktiia smartphone application to a research portal specific for this study.

### Other measures

*Neighborhood environment (SDOH)* We will use the geographic information system tool, PolicyMap, to extract neighborhood-level built environment and social environment characteristics based on participants’ home addresses. We will extract neighborhood-level (e.g., at zip code-level or census track-level) social environment characteristics, including demographic indicators such as racial composition, diversity index (i.e., probability that two individuals chosen at random would be of different races/ethnicities), segregation (Theil index); neighborhood income and poverty, education attainment, employment and unemployment, and crime rate. We will also extract built environment characteristics such as park density, supermarket density, and fast-food restaurant density.

*Covariates* We will ask participants to complete a one-time online survey to assess their demographic information (e.g., age, education level, marital status, employment status, and household income), health literacy, past exposures to lifetime discrimination, and usual diet pattern. These variables will be used as covariates in our statistical models, as needed, and will be helpful in comparing our findings with previous studies and other larger population cohorts.

### Statistical considerations

Multilevel linear mixed-effect models will be used to account for repeated measures (for daily behaviors and daily experience) within an individual. We will separate the between-person and within-person effects by partitioning the variance. **Aim 1**: The daily experience predictors include (1) racial discrimination (i.e., daily EOD and GRMS score), (2) mood/affective states (i.e., daily average of positive and negative affect), (3) daily stress (i.e., daily average of perceived stress and diurnal cortisol rhythm such as total cortisol output, cortisol awakening response, diurnal cortisol slope). The daily behavior outcome variables include total daily moderate-to-vigorous physical activity minutes, total sedentary minutes, and sleep variables (i.e., SOL, WASO, TST). We will link the predictor and outcome at the day-level so that the acute impact of daily experience on behaviors can be examined. **Aim 2**: Outcome variables are indicators of cardiovascular health from lab-based measurements. We will first test the direct independent effects of daily behaviors on cardiovascular health outcomes using the mixed-effect models. Next, we will add the single-level and cross-level interaction terms to each multilevel mixed-effect model to test the moderation effects of daily experience. **Aim 3**: We will test the direct independent effects of neighborhood-level characteristics (predictors) on daily behaviors and daily experience (outcome variables) using the mixed-effect models. All tests of the hypotheses will be two-sided and an alpha level of 0.05. All analyses will be performed using SAS 9.4.

*Sample size and power* Statistical power for evaluation of this study’s objectives was calculated using the macro by Westfall et al. that achieves power estimations based on linear mixed models [56]. Power calculations were computed based on a “fully-crossed” repeated measures design with a two-sided alpha of 0.05. This study will enroll 80 participants. Table 1 displays the statistical power based on possible effect sizes based on adjusted Cohen’s *d* values. Although pilot studies are commonly underpowered, adequate power will be achieved if our study effect is greater than *d* = 0.30. This estimate is indicative of a high likelihood of the planned sample size’s statistical power. We anticipate minimal missing data in the study. However, in the unlikely case of considerable missing data, we will conduct sensitivity analysis to account for different missing data mechanisms (missing at random or missing not at random), using appropriate approaches, such as multiple imputation, pattern-mixture, or selection models [57].

**Table 1 Tab1:** Effect sizes and statistical power yields for *n* = 80

Effect Size		Small			Moderate
Cohen’s *d**	0.10	0.20	0.30	0.40	0.50
Statistical Power (1-*b)*	0.17	0.51	0.84	0.98	0.99

*adjusted for repeated and correlated observations

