## Methods

### Participants recruitment and eligibility

Black women (*n* = 80) will be recruited from the Dallas-Fort Worth Metroplex (Black residents make the 3rd largest racial group in this area). The research team will collaborate with local organizations, including the Tarrant County Health Equity Alliance [31], to assist with recruitment efforts. Study information will be shared at community events, newsletters, and email listservs. The research team will also apply strategies previously identified by scholars with expertise in recruitment and collaboration with Black women [32–34]. Participants can also be recruited from the University of Texas at Arlington (UTA) campus (e.g., students and staff) and through focused social media advertisement (e.g., filtered by geographic location, age, gender).

Interested women will complete a brief online screener to determine eligibility. To be eligible, participants must be assigned female at birth; between 18 and 49 years old; self-identify as Black or African American; not currently pregnant; ownership of a smartphone; and able to speak and read English. *Exclusion criteria* include diagnosed hypertension, cardiovascular, respiratory, metabolic, and/or neurological disorders; functional limitations or health issues that preclude physical activity; currently taking medications for thyroid function or psychological conditions such as depression, anxiety, and mood disorders; current use of oral or inhalant corticosteroids for asthma; or have regularly smoked within the last 2 years.

Recruitment for the study started in February 2024. The first study participant was enrolled on March 4th, 2024. As of May 2024, a total of 63 women completed the eligibility screener, and 27 of them were eligible for the study. Among women who were not eligible for the study, main reason was their current medication use (*n* = 15), followed by medical conditions (*n* = 12) and smoking status (*n* = 4). This study is currently enrolling participants, and we expect to finish study enrollment around October 2025.

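### Aim 3 tests ZIP- or tract-level predictors with models whose only stated clustering is within the woman, so its standard errors will be too small to the extent that women share areas

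*Protocol article*

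**What the plan says.** The Statistical considerations section of the protocol article opens with the purpose of the models: "Multilevel linear mixed-effect models will be used to account for repeated measures (for daily behaviors and daily experience) within an individual". It then separates between-person from within-person effects, which makes two levels: day and woman.

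For Aim 3 the same section says: "We will test the direct independent effects of neighborhood-level characteristics (predictors) on daily behaviors and daily experience (outcome variables) using the mixed-effect models". No area random effect or area-clustered variance is described, and none is ruled out.

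Other measures leaves the area unit open: "We will extract neighborhood-level (e.g., at zip code-level or census track-level) social environment characteristics". The values are assigned from home addresses.

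On the sample, "This study will enroll 80 participants", who "will be recruited from the Dallas-Fort Worth Metroplex". A campus is an additional source: "Participants can also be recruited from the University of Texas at Arlington (UTA) campus". Neither the campus share nor the number of areas expected is given. The Introduction words Aim 3 as exploratory but attaches a hypothesis to it, and the two-sided 0.05 level is set for all hypothesis tests.

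**The concern.** A neighbourhood predictor takes one value for every woman in an area. A random intercept for the woman stops her 10 days from counting as 10 independent observations. It does nothing about correlation between women who live in the same place. If that correlation is positive, the standard error of the neighbourhood slope is understated, and tests at 0.05 reject too often.

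The article's own reasoning makes some residual correlation plausible. The Introduction cites ambient noise and bright light as neighbourhood influences on sleep, and neither is among the characteristics named for extraction. Sharing of areas is also plausible: recruitment runs partly through a county-based organisation, local events and one campus, and both visits take place at that campus. Leaving the unit open matters too, because ZIP codes would produce more sharing than tracts.

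At stake is the credibility of any neighbourhood association that the study reports, since the results are meant to inform interventions that include the social-environmental level.

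**Working it through.** **The plan's own figures.** Nothing in the article quantifies area clustering. Table 1 gives power for 80 women but not the variance components behind it, so it cannot be rebuilt from what is stated. It has no area term and does not bear on this point.

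**Inputs from the article.** 80 women, 10 days, two-sided 0.05, predictor constant within area.

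**Assumptions, not in the documents.**
- Area share of between-woman variance, ρ: 0.05, 0.10 or 0.20.
- Between-woman share of daily variance: 0.40.
- Women fall at random into K equally likely areas.

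**Step 1: area correlation of a woman's 10-day mean.** ρ* = ρ × 0.40 / (0.40 + 0.60/10) = 0.870ρ, which is 0.043, 0.087 and 0.174.

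**Step 2: sharing.** The expected size of the area that a randomly chosen woman lives in is m = 1 + 79/K. K is the pool of areas, not the number represented. The expected number represented is K[1 − (1 − 1/K)^80], about 10, 20, 35, 51 and 66 for K = 10, 20, 40, 80 and 200.

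**Step 3: approximate design effect.** DE = 1 + (m − 1)ρ*. For K = 20 and ρ = 0.20: 1 + 3.95 × 0.174 = 1.69, and √1.69 = 1.30.

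**Step 4: simulation with no true effect.** There were 4,000 runs per cell. The test was the woman-level one, which with balanced days equals a model with a woman random intercept only. Entries are for ρ = 0.05 / 0.10 / 0.20.

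| K | m | DE | True SE ÷ model SE | Type I error (%) |
|---|---|---|---|---|
| 10 | 8.90 | 1.34 / 1.69 / 2.37 | 1.18 / 1.30 / 1.56 | 9.5 / 13.4 / 20.9 |
| 20 | 4.95 | 1.17 / 1.34 / 1.69 | 1.08 / 1.15 / 1.28 | 7.4 / 8.4 / 12.4 |
| 40 | 2.98 | 1.09 / 1.17 / 1.34 | 1.06 / 1.09 / 1.15 | 6.6 / 6.9 / 8.6 |
| 80 | 1.99 | 1.04 / 1.09 / 1.17 | 1.03 / 1.03 / 1.08 | 5.4 / 6.1 / 6.7 |
| 200 | 1.40 | 1.02 / 1.03 / 1.07 | 1.02 / 1.00 / 1.03 | 5.4 / 5.1 / 5.8 |

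With ρ = 0 the error rate is about 5% throughout. √DE tracks the simulated ratios. The Monte Carlo standard error at 5% is √(0.05 × 0.95 / 4,000) = 0.3 percentage points. A repeat with 20,000 runs per cell agreed to within about 1.1 points.

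**Step 5: understatement of the standard error.** This is 1 − 1/ratio. With 10 areas it is 15% (1 − 1/1.18) to 36% (1 − 1/1.56). With 80 areas it is at most 7% (1 − 1/1.08).

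**The case against.** The strongest reply is that this is a condensed article. It calls the models multilevel, does not exclude an area level, and could leave the random-effects structure to a full protocol or analysis plan that is not shown. That is fair as far as silence goes. The point does not rest on silence, however. The article says which correlation the models handle, names the between- and within-person split, and reuses those models for predictors that vary at another level.

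The second reply is that the harm needs two quantities that the article does not give. The catchment is a whole metropolitan area. Areas are assigned by home address, so recruiting someone on campus does not place her in a campus neighbourhood. Individual covariates, used as needed, may absorb part of any area correlation. All of this stands, and it is why the point is conditional and the range starts at essentially no inflation.

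The third reply is that Aim 3 is exploratory and the power paragraph places the study among pilot studies. This also stands and lowers the weight. It does not remove the point, because Aim 3 carries a hypothesis and the 0.05 level is not waived for it.

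**Conclusion.** The concern holds in conditional form and is minor. Followed as written, the Aim 3 model lacks the level at which its predictor varies. The consequence runs from about nil, if the women are widely scattered, to type I error of roughly 7% to 12% with 20 areas. It is higher only with very few areas. These figures depend on the assumed intraclass correlations, variance share and even spread of women over areas.

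A reader might infer three stronger things that the documents do not support.

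- That the standard errors are certainly too small. This needs both shared areas and positive residual correlation, and neither is documented.
- That the effective sample size is the number of neighbourhoods. Take 20 areas of 4 women, with the correlation expressed for the woman's mean. The effective size is 80/(1 + 3 × 0.05) = 80/1.15, about 70, at 0.05, and 80/(1 + 3 × 0.20) = 80/1.60 = 50 at 0.20. It falls to 20 only when the correlation is 1. The days are not counted as independent either, since the woman-level term deals with them.
- That a campus group could produce the slope by itself. No campus share is given, and no influence calculation supports this.

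**What to change.** In the Aim 3 part of Statistical considerations, or in the analysis plan:

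- Name one area unit, ZIP code or census tract, before analysis.
- Fit days within women within areas, with an area random intercept and degrees of freedom that reflect the number of areas (Kenward–Roger, for example). If areas are too sparse for that variance to be estimated, use area-clustered standard errors with a small-sample correction. State the rule for switching in advance.
- Report the number of distinct areas and the distribution of women per area beside the Aim 3 results. These are descriptive and should not be presented as the Aim 3 sample size.
- Optionally, add a sensitivity analysis that excludes or adjusts for campus recruits.

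The cost is one model term or variance option and a few lines of text. Home addresses are already used, so no new data are needed. The downside is slightly wider Aim 3 intervals. If sharing proves sparse, the results will hardly change.

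### Total cortisol output and diurnal slope draw on late-day saliva samples, so their same-day link to activity and sedentary time cannot be read as an acute effect of stress on behaviour

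*Protocol article*

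**What the plan says.** All points are from the protocol article; no separate statistical analysis plan is at hand.

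- **Predictors** (Statistical considerations, Aim 1). The daily stress group holds "daily average of perceived stress and diurnal cortisol rhythm such as total cortisol output, cortisol awakening response, diurnal cortisol slope". No formula is given for any cortisol index.
- **Outcomes and linkage** (same section). Outcomes are daily minutes of moderate-to-vigorous physical activity (MVPA), sedentary minutes, and three sleep variables: onset latency (SOL), wake after onset (WASO) and total sleep time (TST). Predictor and outcome are matched by day so that the acute effect of experience on behaviour can be studied. Within-person and between-person effects are to be separated.
- **Direction** (Introduction, aim 1). Higher stress is expected to lead to more sedentary time that day and worse sleep that night.
- **Saliva schedule.** Study procedures: "They will provide four saliva samples a day for 3 consecutive days out of the 10-day period". The salivary cortisol paragraph sets the samples at waking, 30 minutes later, "before dinner, and right before bedtime", and requires two weekdays and one weekend day.
- **Behaviour coverage** (Ambulatory assessments). "Participants will wear the ActiGraph device on their non-dominant wrist at all times for 10 days".
- **Power** (Sample size and power). "This study will enroll 80 participants". One table serves all objectives, with d "adjusted for repeated and correlated observations". The number of occasions behind it is not stated.

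**The concern.** The linkage rule takes cortisol as the cause and same-day behaviour as the effect. Two of the three named indices are normally built from samples that run to the end of the day. When the bedtime sample is taken, the day's MVPA and waking sedentary time are essentially complete; when the pre-dinner sample is taken, much of them is. Activity or inactivity during the day could itself move those samples, and the same-day model cannot tell the two directions apart. A significant coefficient could then be reported as stress changing behaviour when the reverse had happened.

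There is also a question of precision. Cortisol exists on three days per woman and behaviour on ten, yet the article describes both under one day-level linkage and one power table.

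**Working it through.** **1. The plan's own power figure.** Table 1 gives 0.84 at d = 0.30 with n = 80 and two-sided alpha 0.05. The stated inputs do not fix this value. A one-sample or paired-difference t-test with n = 80 gives 0.755. A paired design with an assumed correlation of 0.6 gives 0.167, 0.506, 0.842, 0.977 and 0.999 across the five effect sizes, against 0.17, 0.51, 0.84, 0.98 and 0.99 in the table. The table is therefore attainable, but that match contains no number of days and cannot be carried over to a 3-day predictor.

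**2. How much the late samples count.** Assume samples at 0, 0.5, 11 and 15.5 hours after waking (the article gives no clock times) and a trapezoid area for total output. The intervals are 0.5, 10.5 and 4.5 hours, so the weights are:

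- waking: 0.5/2 = 0.25
- 30 minutes: (0.5 + 10.5)/2 = 5.5
- pre-dinner: (10.5 + 4.5)/2 = 7.5
- bedtime: 4.5/2 = 2.25

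The two late samples carry (7.5 + 2.25)/15.5 = 63% of the index. A waking-to-bedtime slope, (bedtime − waking)/15.5, rests on the bedtime sample directly. On these times 11/15.5 = 71% of the waking day has passed at the pre-dinner sample and all of it at bedtime. The awakening response uses only the first two samples.

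**3. Effect of reverse timing.** Simulation: 80 women, 3 days, 2,000 runs per setting, person-centred regression, cortisol given no effect on behaviour. Daytime behaviour shifts both late samples by b SD. Rejection rates of a nominal 5% test:

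| b | Total output, same-day behaviour | Slope, same-day behaviour | Awakening response, same-day behaviour | Total output, next sleep | Slope, next sleep |
|---|---|---|---|---|---|
| 0 | 4.4% | 4.9% | 5.2% | 4.8% | 4.6% |
| 0.1 | 25.2% | 13.4% | 4.5% | 5.2% | 5.0% |
| 0.2 | 71.7% | 45.2% | 4.8% | 4.8% | 4.9% |
| 0.3 | 96.2% | 77.2% | 4.9% | 4.4% | 4.7% |

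The values of b are illustrative. Sleep was generated independently of behaviour, so the last two columns show only that the sampling order does not by itself create a false signal there.

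**4. Coverage and precision.** Person-days: 80 × 10 = 800 for behaviour and at most 80 × 3 = 240 for cortisol (30%). Within-person information is proportional to N(T − 1): 80 × 9 = 720 against 80 × 2 = 160. The ratio of standard errors is √(720/160) = √4.5 = 2.12. The standardised within-person slope detectable with 80% power is (1.96 + 0.84)/√[N(T − 1)]: 2.80/26.83 = 0.104 on ten days and 2.80/12.65 = 0.221 on three. This assumes complete data and equal variances across days.

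**5. Weekend.** Of the seven possible runs of three consecutive days, Monday–Wednesday, Tuesday–Thursday and Wednesday–Friday hold no weekend day; Friday–Sunday and Saturday–Monday hold two; only Thursday–Saturday and Sunday–Tuesday hold exactly one. One of each woman's three cortisol days is therefore always a weekend day at the edge of the window, and weekend status forms a sizeable part of her within-person contrast.

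**The case against.** The strongest replies, and what stands of each:

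- **Sleep is correctly ordered.** Three of the five outcomes are sleep variables, and the Introduction places the effect on the night that follows. The bedtime sample precedes that sleep. This stands: the point is confined to MVPA and sedentary minutes.
- **No formula is given, and some behaviour follows the pre-dinner sample.** Both are true. That slope and total output use the late samples is an inference from the schedule, though neither index can span the day without them. Evening sedentary time does come after the pre-dinner sample, and the article gives no clock distribution of behaviour. This softens the point for that sample, not for the bedtime one.
- **Same-day averages of stress and affect share the weakness.** They do in part, because the six daily prompts run to the evening. The 10-day models should not be taken as free of the problem.
- **Three days of saliva is not an error.** Agreed. A mixed model can be fitted to those days, and all 80 women still inform the between-woman effect.
- **The weekend pattern is minor.** The weekend day can come first or last, so it is not tied to sampling order across women, and an indicator is a routine covariate. It is a small addition to the fix.

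A reader might also infer that 70% of the Aim 1 data will be discarded because perceived stress and cortisol are listed together. The article lists constructs; it nowhere says they enter one equation. That loss would arise only in a joint model that is not stated.

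**Conclusion.** The point holds for two cortisol indices, total output and diurnal slope, against two outcomes, same-day MVPA and sedentary minutes. For these pairs the day-level rule cannot support the causal direction that the article gives it. The possible false-positive rate is large under modest reverse effects (13% to 96% over the range tried), but those effect sizes and the clock times are assumptions. The awakening response and the following night's SOL, WASO and TST are outside the point.

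The cortisol tests also have lower within-person precision: at most 240 of 800 person-days and a standard error about 2.1 times larger with complete data. It is tempting to go further and say that the stated power of 0.84 falls to about 0.29. That figure comes from (0.99 + 1.96) × √(2/9) − 1.96 = −0.57, and it requires Table 1 to describe a within-person slope on ten days. The article does not say so, and the table could not be reproduced from its stated inputs. The supported statement is narrower: Table 1 should not be assumed to cover the cortisol tests.

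**What to change.** 1. For same-day MVPA and sedentary minutes, use only the morning cortisol measures: waking level and awakening response.
2. Use diurnal slope and total output for that night's sleep, for next-day behaviour, or as a 3-day mean in a between-woman analysis. If same-day results for them are kept, label them as associations without direction.
3. State that cortisol models are fitted on the three sampled days, separately from the 10-day models, and include a weekend indicator.
4. State the coverage (at most 240 of 800 person-days) and the lower within-person precision, and say that Table 1 is not claimed for these tests unless its number of occasions is given and matches.

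Cost: wording of the analysis only, with no new data. The same-day slope and output results are lost or lose their directional reading, and the cortisol results are presented with openly wider intervals.
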